In today’s social arena, application of the Artificial Intelligence Health Education Accurately Linking System (AI-HEALS), an artificial intelligence-based health education system on WeChat, the largest social media in China, is especially significant. AI-HEALS uses economical and ubiquitous mobile communication technology, which enables patients to easily obtain ongoing disease care and management from home. Interventions in AI-HEALS are based on the integrative Health Behavior Promotion Model (HAPA-MTM), which not only supports physical symptoms management in patients but also focuses on mental health and behavior change, ultimately providing an all-encompassing and long-term management approach (15, 16). Its main features involve AI-based Q&A based on an in-house knowledge database, physiological indicator tracking and behavior monitoring, various reminder services, and customized information delivery. This new intervention model is more adaptable to cater to health management requirements of contemporary society, with an effective support and management solution for COPD patient population, and demonstrating the potential of emerging technology in health management.

In summary, this study proposes to assess the efficacy of AI-HEALS intervention in managing one’s own health in COPD patients by conducting a randomized controlled trial (RCT), with special emphasis on the following:

Evaluate the efficacy of a 3-months intervention program based on the AI-HEALS in enhancing physiological markers in COPD patients;Assessing the efficacy of a 3-months multidisciplinary intervention program based on AI-HEALS to improve psychological markers among COPD patients;Assess the efficacy of a 3-months multifaceted intervention program based on the AI-HEALS to enhance self-management behaviors among COPD patients.

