#### Secondary outcomes

2.8.2

Changes in self-management behaviors: including diet, physical activity, medication adherence, smoking management, alcohol management, sleep management, quality of life, and activities of daily living.

Social Cognition and Psychological Factors: COPD knowledge literacy, self-efficacy, depression, anxiety, stress, and social support.

Control of physiological indicators: cough, breathlessness, blood pressure, height, and weight.

30-days readmission rate: additionally, recruitment rates, dropout rates, and reasons for withdrawal will be collected. To assess the homogeneity of the data, demographic characteristics and outcomes of those who dropped out, as well as those with resistance to the trial, will be compared during the data analysis process.

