### Statistical analysis

2.11

We will collect quantitative data using a structured questionnaire and then input it into Microsoft Excel for analysis. All major analyses will follow intention to treat (ITT) and will undergo protocol compliant (PP) analysis for sensitivity testing. Descriptive statistics will be used to summarize feasibility variables such as starting information, number of participants, and system usage. For continuous data, the mean and standard deviation of normally distributed data, as well as the median and 25th to 75th percentile of non-parametric data, will be provided. To compare the untreated group and the group measured once, independent sample *t*-tests and their non-parametric analogues will be used. The categorical data will be expressed in frequency and percentage, and analyzed using chi square test. The normality of the data will be tested using the Kolmogorov Smirnov test. Under the assumption of random missing data, established multiple imputation methods will be used in appropriate circumstances to handle the missing data. We will examine and compare the missing and wear patterns between each group to identify potential differences in dropout rates, and conduct sensitivity analysis to compare estimated and complete case outcomes. For the main experiments, the focus will be on using a linear mixed effects model to evaluate the main outcome indicators. For secondary outcomes such as self-management and psychosocial/cognitive outcomes, analysis will use similar mixed effects models or simpler comparison methods, depending on the nature and timing of data collection. In addition, exploratory age stratification analysis can be conducted to examine the potential heterogeneity of intervention effects across different age groups in a descriptive manner. Given the pilot nature of the study, the results should be interpreted with caution. The measurement criteria used by the system, such as the number of questions, will be summarized in a descriptive manner and can be included as covariates in exploratory analysis to better understand compliance patterns; these analyses will be seen as hypothesis generation rather than validation. All statistical tests are two-sided, with a significance level of 0.05. Data analysis will be conducted using IBM SPSS Statistics (version 24.0; SPSS Inc., Chicago, Illinois, USA and Stata (version 14.0); StataCorp, College Station, TX, The United States) conducted.

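### The efficacy objectives rest on secondary outcomes that section 2.11 tests at 0.05 without calling them exploratory, although section 2.4 says the pilot is not primarily for hypothesis testing

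*Protocol article*

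**What the plan says.** **Objectives (protocol article, Introduction).** There are three, each worded as efficacy: "Evaluate the efficacy of a 3-months intervention program based on the AI-HEALS in enhancing physiological markers in COPD patients"; "Assessing the efficacy of a 3-months multidisciplinary intervention program based on AI-HEALS to improve psychological markers among COPD patients"; and "Assess the efficacy of a 3-months multifaceted intervention program based on the AI-HEALS to enhance self-management behaviors among COPD patients". None names an outcome that decides it, and none names the CAT.

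**Outcomes (2.8.1 and 2.8.2).** The single primary outcome is change in CAT. The secondary outcomes fall into blocks that match the objectives:
- Physiological, five items: "Control of physiological indicators: cough, breathlessness, blood pressure, height, and weight".
- Psychological and cognitive, six items: "COPD knowledge literacy, self-efficacy, depression, anxiety, stress, and social support".
- Self-management, eight items, from diet to activities of daily living.

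**Visits (2.9 and Table 1).** Measurements are repeated at discharge, at the end of the intervention, and 3, 6 and 9 months later. Table 1 omits discharge for EQ-5D-5L, smoking, alcohol and sleep.

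**Analysis (2.11).** The testing rule is "All statistical tests are two-sided, with a significance level of 0.05". Secondary outcomes get mixed models or simpler comparisons, depending on the data. The age strata are called exploratory, and of the system-usage analyses it says "these analyses will be seen as hypothesis generation rather than validation". One general sentence asks for caution because the study is a pilot.

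**Purpose of the pilot (2.4).** Its primary objective is to estimate variance and effect size and not to test hypotheses. Its estimates feed the sample size of a later main trial, which is to be powered for the study hypotheses.

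**The concern.** The document gives two answers to one question: are the secondary outcomes in this 60-patient phase tested or estimated? Section 2.4 points to estimation. The objectives and the blanket 0.05 rule point to testing.

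The primary/secondary split does not settle it. The CAT appears in none of the three objectives, so the stated aims are answered entirely by secondary outcomes. Section 2.11 does use exploratory labels, but on other analyses, which leaves a reader to suppose that the unlabelled secondary outcomes have a different standing.

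At stake is what the pilot report may say about its own objectives. With several scales per objective, several visits and no deciding outcome, a sentence claiming efficacy on psychological markers could rest on whichever result happened to cross 0.05. Participants are unblinded and most outcomes are self-reported (2.2, 2.10, Discussion), which makes such a claim weaker still.

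**Working it through.** **1. The passages side by side**

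| Place | Points to |
|---|---|
| Introduction, objectives | efficacy conclusions on three domains |
| 2.8.1 | CAT as the only primary outcome, in none of the three objectives |
| 2.11, testing rule | a 0.05 test for every outcome |
| 2.11, exploratory labels | age strata and system usage only |
| 2.11, caution sentence | careful reading of results; no test withdrawn |
| 2.4 | estimation in the pilot; hypothesis tests in the main trial |

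The first and third rows cannot both hold for the pilot if the last row governs it.

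**2. The plan's own figure**

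One test at two-sided 0.05 has a false-positive chance of 1 − 0.95 = 0.05. This is the only error rate in the protocol, and it applies to a single test.

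**3. Outcomes per objective**

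I counted only outcomes that have a scheduled instrument or a described measurement and that can change:
- Physiological: cough, breathlessness, blood pressure and weight (4; height is left out).
- Psychological: PHQ-4, PSSS-SF and NGSES-SF (3, or 4 if PHQ-4 is split into depression and anxiety).
- Self-management: smoking, alcohol, sleep and EQ-5D-5L (4).

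So k is 3 or 4.

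**4. One test per outcome, no true effect**

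The quantity is the chance that at least one of k tests has p < 0.05. It bears on an objective only under the assumption that one significant outcome would be read as efficacy on it.

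- Independent tests: 1 − 0.95^k. For k = 3 this is 1 − 0.8574 = 0.143. For k = 4 it is 1 − 0.8145 = 0.185.
- Equally correlated normal test statistics with correlation ρ: 1 − E[{Φ((1.96 − √ρ·U)/√(1−ρ)) − Φ((−1.96 − √ρ·U)/√(1−ρ))}^k], with U standard normal.

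| k | ρ = 0 | ρ = 0.5 | ρ = 0.8 |
|---|---|---|---|
| 3 | 0.143 | 0.125 | 0.098 |
| 4 | 0.185 | 0.156 | 0.114 |

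The range is 0.098 to 0.185, about 10% to 19%. The documents give no correlations, so ρ is an assumption.

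**5. Every visit tested as well**

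I simulated normal statistics with assumed correlation 0.5 between outcomes and 0.7 between visits, and counted draws with any |Z| > 1.96:
- 3 outcomes at 5 visits: about 34%.
- 4 outcomes at 4 visits: about 37%.
- 4 outcomes at 5 visits: about 41%.

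The 10% to 19% in step 4 does not include the repeated visits. The 34% to 41% does, and it holds only if each visit were tested separately, which section 2.11 permits but does not state.

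**The case against.** **Multiplicity among secondary outcomes is commonly left to the analysis plan, which is not shown.** This stands: the lack of an alpha split or testing order is no finding. What remains is how the statements in this document fit together: efficacy objectives, 0.05 for every test, and a pilot not primarily meant for testing.

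**There is a hierarchy and a caution.** This is also correct. The CAT is the one primary outcome, the rest are secondary, and section 2.11 asks for caution because of the pilot. But the hierarchy does not reach the objectives, and the caution neither removes a test nor names a secondary outcome as exploratory.

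**The objectives may belong to the two-phase programme, with efficacy settled in the main trial.** This is a reasonable reading, and section 2.4 favours it. The Introduction does not say so, however, and section 2.11 applies its rule while referring to the study as a pilot.

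**A stronger reading.** A reader might infer that the protocol lets any p < 0.05 at any visit establish an objective, so that its stated 5% error is inflated threefold or more. The documents do not support this. The 5% is a level per test, not a rate per objective. No section says that one significant result meets an objective. Section 2.11 does not say that each visit is tested separately, and a mixed model could yield one test per outcome.

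**Conclusion.** The concern holds as an inconsistency between the objectives, section 2.11 and section 2.4. The secondary outcomes that carry all three efficacy objectives are to be tested at 0.05 and are not labelled exploratory, in a phase whose stated main purpose is estimation.

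The percentages describe a way of reading the results that the protocol leaves open, not one that it prescribes. If one significant outcome were taken as efficacy on an objective, a false claim would occur about 10% to 19% of the time with one test per outcome, and about 34% to 41% with every visit tested. Both ranges depend on my outcome counts and assumed correlations. The point is worth correcting because it decides what the pilot can conclude on its own objectives.

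**What to change.** - **Section 2.11:** state that in the pilot phase all secondary outcomes are exploratory at every visit and will be reported as estimates with 95% confidence intervals, without significance claims.
- **Introduction:** reword the three objectives for the pilot phase as estimating the effect of AI-HEALS on physiological, psychological and self-management outcomes, in line with section 2.4.
- **Confirmatory claims:** leave these to the main trial. The pilot needs neither a multiplicity procedure per objective nor a statement that the CAT establishes efficacy; the latter would itself conflict with section 2.4.

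The cost is a few sentences and no new data. The downside is that fewer secondary results can be called significant.

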## Study management

3

### Ethical oversight, data monitoring, and trial governance

3.1

A Data Monitoring Committee (DMC) will be established, consisting of at least two members from the Ethics Committee of the First People’s Hospital of Zigong who have no conflict of interest with this study. The committee will conduct routine review and monitoring of research progress and report directly to the ethics committee to ensure its independence from the principal investigator. If any unauthorized deviation from the plan or unauthorized changes are found during the monitoring process, DMC has the right to suspend or terminate the trial.

The hospital ethics committee will conduct a formal review every 6 months to evaluate the progress of the trial and ensure compliance with the approved protocol. All proposed modifications must first be reviewed by the steering committee. After approval, the proposed changes will be submitted to the hospital ethics committee and research department for further review and approval. After approval, a formal document detailing the revised content will be distributed to all relevant parties, and electronic versions will be provided if necessary. All changes to the protocol will be recorded by the trial coordinator and confirmed by the main researcher’s signature. The relevant documents will be archived together with other trial materials. After all approval procedures are completed, the clinical trial registration information will be updated synchronously.

### Trial conduct, team communication, and safety monitoring

3.2

Prior to trial initiation, the principal investigator (PI) will hold weekly meetings with the trial team to ensure that all study procedures strictly adhere to protocol requirements. During the data collection phase, trial team meetings will be conducted on a monthly basis. In addition, the PI and trial manager will maintain daily communication throughout the study to confirm protocol compliance and address any operational issues promptly.

During the course of the study, if there’s an adverse event (AE) or severe adverse event (SAE), the Ethics Committee must be notified immediately. If the participant suffers from an AE or SAE, with or without relation to the research, the research team must notify the Ethics Committee within 24 h and, if necessary, halt the experiment. In the event of severe errors regarding the AI’s programming and/or severe technological issues regarding the use of the AI, the experiment will be halted instantly. The experiment will only proceed with the redesign and continuation after all the technological issues have been resolved.

### Training, protocol adherence, and data quality control

3.3

Before the study commences, training workshops and assessments will be conducted by domain experts to ensure that all research team members are fully familiar with study procedures and technical requirements. To minimize loss to follow-up, all participants will be recorded and assigned unique identification codes. To maintain consistency between the intervention and comparison groups, all survey periods will be identical, and the same questionnaires will be administered across all time points.

Data quality will be ensured by carrying out double data entry and verifying the data. The selection of the appropriate analysis procedures would be done after consulting statisticians. If there are any errors discovered in the course of data analysis, the final results would be verified by examining the copies of the questionnaire.

### Data management, unblinding, and protocol amendments

3.4

Data management will be conducted by a data administrator who will be responsible for administering the recording of the data, cloud storage of the information, accessing the information, as well as solving any problems. The trial administrator will check the information for accuracy.

Unblinding is only permitted under exceptional circumstances, including medical emergencies whereby it is necessary to know to which group the participant belongs. These circumstances include serious adverse events or emergency medical care. The requirement to know group allocations may also be requested following completion of the study for medical reasons. Every request for unblinding will be written by the PI or a member of the clinical review team. A group of professionals will assess the request to determine whether predefined criteria exist for a requested unblinding. Group allocation information will be exchanged as per predefined procedures to maintain participant safety and integrity.

### AI system validation, safety controls, and knowledge base updating

3.5

Prior to study initiation, the AI-HEALS system will undergo internal validation to ensure the accuracy, consistency, and appropriateness of its educational content. This validation process includes expert review of the COPD knowledge base by clinicians with experience in COPD management, as well as scenario-based testing using common patient questions to verify that generated responses are aligned with established clinical guidelines and predefined educational boundaries.

During the trial, multiple safety control mechanisms will be implemented. The AI-HEALS system is designed to provide health education and self-management support only and does not generate diagnostic or treatment decision-making advice. All responses are constrained to the curated COPD knowledge base to minimize the risk of inaccurate or unsafe outputs. System interaction logs will be monitored regularly by the research team to identify potential anomalies or inappropriate responses, which will be reviewed and addressed in a timely manner.

Procedures for maintaining and updating the knowledge base are established throughout the study period. Updates will be conducted under the supervision of clinical experts and implemented in response to guideline updates, emerging evidence, or identified content gaps. Any modifications to the knowledge base will follow a standardized review process and be documented to ensure transparency and consistency during the trial.

## Dissemination plans

4

A summary of the RCT findings will be prepared by the research team and emailed to trial participants who indicated interest in receiving the results on their consent forms. The study outcomes will be disseminated through peer-reviewed journal publications and presentations at both national and international conferences. Additionally, findings will be made available upon reasonable request, including to other hospitals for use by medical staff (30, 31).

## Discussion

5

This study is designed to systematically evaluate the effectiveness of the AI-HEALS intervention, delivered via the WeChat platform, in improving physiological indicators, mental health, and self-management behaviors among patients with COPD through a randomized controlled trial. Although previous interventions have provided some benefits for patients with COPD, long-term self-management remains challenging due to the complexity of the disease, psychological burden, and limited access to continuous, individualized support (9, 10). Existing mobile health interventions have attempted to address these issues. However, their effectiveness has often been constrained by high dropout rates, complex intervention procedures, or a narrow focus on selected behavioral outcomes (12, 13).

Against this backdrop, the present study integrates a 3-months AI-HEALS intervention grounded in the HAPA-MTM framework with a 9-months follow-up period to evaluate both the effectiveness and sustainability of behavior change. The use of artificial intelligence enables the delivery of tailored, timely, and scalable health education, while the integration with WeChat, a widely adopted communication platform, may enhance accessibility and user engagement. By addressing gaps in the literature regarding the long-term sustainability and practicality of digital self-management interventions for COPD, this study aims to contribute empirical evidence supporting the role of AI-enabled tools in chronic disease management.

Several limitations of this study should be acknowledged. First, the single-center design and reliance on the WeChat platform may limit the generalizability of the findings to other healthcare settings, regions, or cultural contexts. Second, due to the nature of the AI-based behavioral intervention, blinding of participants and intervention facilitators is not feasible, which may introduce Hawthorne effects and bias in self-reported outcomes; although standardized procedures and objective indicators are applied where possible, such bias should be considered when interpreting the results. To prevent cross-contamination between groups, participants are allocated to different hospital ward according to their assignments. While this approach helps maintain intervention fidelity, it may introduce potential allocation or environmental bias related to ward-specific contextual factors, despite standardized care protocols across ward. In addition, variations in digital literacy among participants may influence engagement with the intervention, although simplified system features, such as voice input and automated prompts, are incorporated to reduce operational barriers. As digital health literacy is not formally measured, its impact will be interpreted cautiously. Finally, this trial focuses primarily on clinical, psychological, and behavioral outcomes, and does not include formal health economic evaluation. The long-term sustainability of the AI-HEALS system, including cost-effectiveness and knowledge base maintenance, warrants further investigation in future studies.
